**Setting:**

Three clinical units of the Department of Critical Care Medicine at the First Hospital of Jilin University (Changchun, China).

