### Sample size

2.5

The sample size was estimated in PASS v23 (NCSS, Kaysville, UT; https://www.ncss.com/software/pass/) for the primary endpoint of energy intake on day 7 (kcal/kg/day), comparing two independent groups with equal allocation (1:1). Based on retrospective data, the SPF group had a mean ± standard deviation (SD) intake of 22.4 ± 9.825 kcal/kg/day and the PBF group had 24.9 ± 9.1 kcal/kg/day. Using a two-sided *α* = 0.05 and power (1 − *β*) = 0.90, the required sample size is *n* = 225 per group (total *N* = 450). Allowing for a 10% attrition rate, the target sample increases to *N* = 495. To maintain balance between the two treatment groups under block randomization with variable block sizes of 4 and 6, the final planned sample size is *N* = 496.

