#### Secondary outcome definition and measures

2.7.2

Protein intake on Day 7, defined as the actual protein delivered on study Day 7 (g/kg/day). For patients with BMI > 30 kg/m^2^, an AdjBW will be used.Occurrence of FI between ICU days 4–7, FI is defined as (6) present if any of the following criteria are met: ① Vomiting: any visible regurgitation of gastric contents, irrespective of volume. ② High gastric residual volume (GRV): any single GRV > 200 mL. ③ Diarrhea: ≥3 loose or liquid stools per day and stool weight >200–250 g/day or volume >250 mL/day. ④ Gastrointestinal (GI) bleeding: any intraluminal GI bleeding confirmed by gross blood in vomitus, gastric aspirate, or stool. ⑤ Insufficient enteral energy delivery: failure to achieve ≥20 kcal/kg body weight/day via the enteral route within 72 h after initiation/attempt of enteral feeding. ⑥ Cessation of enteral nutrition: enteral feeding discontinued for any clinical reason. Outcome recording. The presence or absence of FI will be assessed once per day on ICU days 4–7. In addition to the composite FI outcome, individual FI components will be reported and analyzed separately.Change in nutritional biomarkers. Defined as serum albumin and prealbumin concentrations measured on study day 1 (baseline) and day 7. Reporting values (albumin in g/L; prealbumin in mg/L) at each time point; change calculated as Day 7 − Day 1.Skeletal muscle status. Muscle mass change will be assessed using the following sonographic metrics on ICU days 1, 4, and 7 after admission: upper-limb muscle thickness; quadriceps muscle thickness; rectus femoris cross-sectional area (RF-CSA).Intestinal injury biomarkers. Between-group differences in intestinal injury markers will be evaluated using serum/plasma concentrations of D-lactate, intestinal fatty-acid binding protein (I-FABP), and diamine oxidase (DAO) on study Day 1 and Day 7. *Measurement & reporting:* assays performed per manufacturer instructions; values reported in assay-specified units. Changes from baseline (Day 7–Day 1) and between-group differences in change will be analyzed.New infections in the ICU: Defined as infections newly acquired ≥48 h after ICU admission.ICU length of stay.Ventilator-free days: Ventilator-free days within 28 days in the ICU.ICU hospitalization cost. Defined as the total direct medical cost accrued during the index ICU stay, from ICU admission (time 0) to ICU discharge. Extracted from the hospital billing system/financial data warehouse using patient identifiers and ICU encounter numbers.28-day mortality: Assessed on day 28 after ICU admission.90-day mortality: Assessed on day 90 after ICU admission.

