##### Exposure metrics

2.7.5.1

All participants receive a short-peptide formula from enrollment through study Day 3; this run-in period is not included in exposure analyses and is used solely for baseline standardization and tolerance assessment. Randomization occurs on Day 4 (D4). The exposure assessment window is D4–D7. We will record:

Duration of the exposure window (hours): elapsed time from randomization (D4) to 23:59 on D7 or to ICU transfer/discharge or death, whichever occurs first.Concordant feeding hours: cumulative hours during which the randomized formulation was actually administered.Adherence (%) = (concordant feeding hours ÷ exposure window hours) × 100. Interruptions (e.g., procedures, intolerance) will be time-stamped; calculations use actual accrued hours within the window.

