#### Data analysis

2.8.2

All statistical analyses will be conducted in accordance with a pre-specified statistical analysis plan. The primary analysis will follow the intention-to-treat (ITT) principle The Full Analysis Set (FAS) will include all participants who were successfully randomized and entered the intervention period, provided that they have a valid assessment of the primary outcome (caloric intake on day 7) or sufficient information to derive this value. The Per Protocol Set (PPS) will be a subset of the FAS, including participants who received the allocated intervention for at least 72 h and had no major protocol deviations. The PPS will be used for sensitivity analyses to assess the robustness of the primary findings. The SS will include all participants who received at least one dose of the study intervention and will be used for safety analyses.

The primary outcome, caloric intake on day 7 (continuous variable), will be analyzed using a linear regression model. The model will include the intervention group and the predefined covariates (APACHE II score, BMI, AGI grade, and primary diagnosis) as fixed effects. As this is a single-center randomized controlled trial, no random effects will be specified. To account for potential model misspecification and heteroscedasticity, heteroskedasticity-robust (sandwich) standard errors will be used for statistical inference. If the model residuals show substantial deviation from normality or are influenced by outliers, data transformation (for example, logarithmic transformation) or a nonparametric bootstrap method will be applied in sensitivity analyses to assess the robustness of the results.

Continuous secondary outcomes (e.g., the number of days without a ventilator in the ICU) will be analyzed analogously using linear regression models; secondary binary outcomes (e.g., FI) will be analyzed using a generalized linear model (GLM) with a logit link function. The model will include the intervention group and the pre-specified covariates as fixed effects. As this is a single-center study without inter-center or clustering structures, no random effects will be specified. In addition, because FI is a composite secondary endpoint, each FI component will be reported and analyzed separately alongside the composite FI outcome.

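### No analysis model contains the outcome's own pre-randomisation value, so the five blood-marker comparisons lose precision that a Day-1 value already collected would give

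*Protocol article*

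**What the plan says.** Section 2.8.2 (Data analysis) defines the primary analysis of Day-7 energy intake as a linear regression with robust standard errors: "The model will include the intervention group and the predefined covariates (APACHE II score, BMI, AGI grade, and primary diagnosis) as fixed effects". Continuous secondary outcomes follow the same approach with the prespecified covariates. Of the sensitivity models, one is unadjusted, one adds baseline mechanical ventilation, and one brings in feeding-process indicators. The covariates are declared prespecified and are kept whatever their significance.

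Section 2.7.2 measures albumin, prealbumin, D-lactate, I-FABP and DAO on Day 1 and Day 7. For the two nutritional markers it specifies "change calculated as Day 7 − Day 1", and the three intestinal markers are likewise compared on change from Day 1. Muscle ultrasound is done on Days 1, 4 and 7, with no visit named as baseline.

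All patients receive the peptide formula on study days 1–3 and are randomised on day 4 (sections 2.4 and 2.6). Section 2.7.5.1 keeps this run-in out of the exposure analyses and says it "is used solely for baseline standardization and tolerance assessment".

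**The concern.** A value of the outcome measured before allocation is usually among its strongest predictors, and here each patient is observed for three days before randomisation. A change score uses the baseline but fixes its coefficient at 1 instead of estimating it. Unless that happens to be the right coefficient, the comparison is less precise than it could be, and part of any chance difference between arms on Day 1 carries into the estimated effect.

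For energy intake, which is analysed as the Day-7 value and not as a change, no earlier intake enters any model. Precision matters here because the sample size in section 2.5 does not deliver the power it states (shown in the working).

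**Working it through.** **1. Blood markers: change score against ANCOVA.** Let s0 and s1 be the SDs on Day 1 and Day 7, and r their correlation. The documents give no r for any marker, so it is assumed.

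- Variance of the change score: s0² + s1² − 2·r·s0·s1
- Residual variance with Day 1 as covariate: s1²(1 − r²)
- Difference: (s0 − r·s1)², which is never negative. Apart from one degree of freedom, ANCOVA cannot be the less precise.
- With s0 = s1 = s the ratio is s²(1 − r²) / [2s²(1 − r)] = (1 + r)/2.

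At r = 0.5 the ratio is 0.75 (variance 25% smaller); at r = 0.7 it is 0.85 (15% smaller). Because the planned models already hold other covariates, r should be read as the partial correlation given them.

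Chance imbalance: with equal SDs, a Day-1 difference D between arms shifts the expected change-score difference by (r − 1)·D, which is −0.5·D at r = 0.5. ANCOVA removes this shift. Over repeated randomisations D averages zero, so the change-score analysis is unbiased.

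**2. Energy intake: the plan's own figure first.** Inputs from section 2.5: "Using a two-sided *α* = 0.05 and power (1 − *β*) = 0.90"; 225 per group; mean (SD) intake in kcal/kg/day of 22.4 (9.825) for SPF and 24.9 (9.1) for PBF.

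- Difference: 24.9 − 22.4 = 2.5
- Sum of variances: 9.825² + 9.1² = 96.53 + 82.81 = 179.34
- n per group for 90% power: (1.960 + 1.282)² × 179.34 / 2.5² = 301.5, so 302. The stated 225 is not reproduced.
- The same formula at 80% power gives 225.2.
- Power at 225 per group: Φ(2.5/√(179.34/225) − 1.96) = Φ(0.840) = 80.0%

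**3. What run-in intake could add.** If run-in intake has correlation r with Day-7 intake, the residual variance is multiplied by (1 − r²) and power becomes Φ(2.5/√((1 − r²) × 179.34/n) − 1.96). The last column uses the roughly 15% missing Day-7 values expected in section 2.8.3: 496 × 0.85 / 2 = 210.8 per group.

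| assumed r | power, n = 225 | power, n = 210.8 |
|---|---|---|
| 0 | 80.0% | 77.4% |
| 0.3 | 83.5% | 81.1% |
| 0.4 | 86.3% | 84.1% |
| 0.5 | 89.9% | 87.9% |
| 0.6 | 93.8% | 92.3% |

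The r needed for 90% is √(1 − 225/301.5) = 0.504 at 225 per group and √(1 − 210.8/301.5) = 0.548 with 15% missing.

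**4. Is run-in intake recorded?** No passage in the text names a Day 1–3 intake variable, and the schedule table is not shown. FI criterion 5 (section 2.7.2) requires enteral kcal/kg/day to be judged within 72 h of starting feeding. That points to recording but does not establish it.

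**The case against.** The planned primary model is valid: a regression with four prespecified covariates and robust standard errors. Leaving out a further covariate cannot bias a randomised comparison, so this is a matter of efficiency. That stands and limits the weight of the point.

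For energy intake, three further objections stand. Recording of run-in intake is an inference. FI criterion 5 covers the enteral route only, whereas the primary outcome is actual caloric intake and parenteral nutrition may be given. And r is unknown: the power table starts as if the four planned covariates explained nothing, while intake early in feeding may predict Day 7 only weakly. It would also be unfair to call the biomarker analyses unadjusted; they carry the prespecified covariates and omit only the marker's own Day-1 value.

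The objection that this is detail for an unseen SAP does not stand. The article itself names the covariates and defines the change from Day 1.

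**Conclusion.** The point holds as a loss of precision. It is firmest for the five blood markers, where the Day-1 value is certainly collected, precedes randomisation and appears in no model as a covariate. The size depends on an undocumented correlation: 25% of the variance at r = 0.5 and 15% at r = 0.7, assuming equal variances.

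A reader might infer that adjusting for run-in intake would restore the stated 90% power. The documents do not support that: it requires a partial correlation of about 0.50 (about 0.55 with 15% missing) in a variable not stated to be recorded. At r = 0.3 to 0.4 power at 225 per group is only 83.5% to 86%. The shortfall to 80% arises in section 2.5 and must be corrected there.

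A reader might also take the Day-4 scan as the natural muscle baseline. Sections 2.6.4 and 2.7.2 do not say that it precedes that day's randomisation. Nor should the sentence on the run-in in section 2.7.5.1 be read as barring its data as covariates; it concerns exposure analyses.

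**What to change.** Before outcome data are analysed:

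- Add the Day-1 value as a covariate in each model for albumin, prealbumin, D-lactate, I-FABP and DAO. Change may remain the reported outcome, because with Day 1 in the model the treatment estimate is the same for change and for the Day-7 value.
- If run-in intake is recorded, add pre-randomisation energy intake (for example Day 3, in kcal/kg/day and covering the same routes as the Day-7 outcome) to the primary model, and protein intake to the protein model. Put the same variables in the imputation model, which section 2.8.3 already leaves open to further predictors.
- For muscle measures, state whether the Day-4 scan is taken before randomisation. If so, use it as the covariate; if not, use Day 1.
- Correct the sample-size statement in section 2.5 separately.

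The cost is a few lines of analysis wording and one degree of freedom per model. The biomarker change needs no new data; the intake change needs none if run-in intake is already captured.

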### Randomization and blinding methods

2.4

Because all enrolled patients initially present with AGI grade I–II, a PBF will be administered for the first 3 study days. On day 4 of the study, gastrointestinal function will be reassessed. Patients reassessed as AGI grade 0–I will be eligible for randomization. Eligible patients will be randomized using block randomization, with a 1:1 allocation ratio to either continued a PBF (PBF group) or transition to an SPF (SPF group). The randomization sequence will be generated in R software (version 4.4.2) using permuted blocks of variable size (4 and 6).

Owing to the nature of the intervention, this is an open-label protocol, and the treating clinical team must be aware of group assignment for intervention delivery (participants may or may not be aware depending on clinical status). To minimize detection bias, feeding intolerance and other outcomes will be assessed and recorded by dedicated research staff who are independent from the ICU clinical team and do not participate in treatment decisions or nursing care.

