This study has several notable strengths. 1. To our knowledge, this is the first large randomized controlled trial to address whether, in critically ill patients with AGI whose intestinal function has recovered or at least not worsened, a transition from a PBF to an SPF is necessary. 2. We selected actual caloric intake as the primary endpoint to directly capture the impact of formula type on achieved nutrition, and we complemented this with a broad set of secondary outcomes—including actual protein intake, feeding tolerance, nutritional serum biomarkers, intestinal injury markers, trajectories of muscle mass, and key clinical endpoints—to provide a comprehensive and systematic evaluation. 3. Conducting the trial at a single center is expected to enhance consistency in the feeding protocol and ultrasound measurements. 4. To reduce heterogeneity and confounding, we excluded patients with hepatic or renal disease and those receiving extracorporeal therapies, conditions known to influence metabolism and nutritional requirements (23). 5. Moreover, clinical data are collected by an independent research team that is not involved in patient care, randomization, or data analysis, thereby minimizing subjective bias.

This study also has important limitations. 1. The single-center design may limit external validity and generalizability. 2. Our primary endpoint—caloric intake on ICU Day 7—introduces a risk of missing data among patients who are discharged or die before Day 7; these cases require imputation, which may deviate from true values. 3. Despite standardized training based on the guideline, some team-level subjectivity in implementation is unavoidable and could affect delivered feeding volumes or tolerance management. Although we will adjust for prespecified covariates, co-interventions and variability in feeding strategies may still influence the results, and residual confounding cannot be excluded. Our findings will be interpreted cautiously. 4. Finally, due to resource constraints, indirect calorimetry was not used to set energy targets, which may reduce the precision of prescribed goals.

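### The stated absence of clustering does not fit a trial run in three ICU units; unit is in no listed model, at a possible small cost in precision but not in validity

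*Protocol article*

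**What the plan says.** The abstract of the protocol article gives the setting as "Three clinical units of the Department of Critical Care Medicine" at one hospital. Section 2.4 randomises individual patients 1:1 in permuted blocks of 4 and 6 and mentions no stratification by unit.

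For the primary outcome, section 2.8.2 specifies a linear regression with robust standard errors: "The model will include the intervention group and the predefined covariates (APACHE II score, BMI, AGI grade, and primary diagnosis) as fixed effects". It adds: "As this is a single-center randomized controlled trial, no random effects will be specified". For the secondary outcomes the reason is stated more strongly: "As this is a single-center study without inter-center or clustering structures, no random effects will be specified". The sensitivity models in the same section add baseline mechanical ventilation and several feeding-management variables, but not unit. The imputation model in section 2.8.3 does not name unit either, although its allowance for further predictors leaves room for it.

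The Discussion, under limitations, says that "some team-level subjectivity in implementation is unavoidable and could affect delivered feeding volumes or tolerance management".

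**The concern.** Being single-centre is a fact about the trial. Having no clustering structure does not follow from it when three units deliver the feeding. The plan's own limitation names a mechanism, team practice, that would act directly on delivered volume and so on day-7 kcal/kg. If practice differs by unit, a baseline variable that explains part of the outcome has been left out, on a stated ground that the rest of the article does not support.

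Two things are at stake. Variation between units stays in the error term of the primary model, and any chance imbalance of units between arms goes uncorrected. The management variables in the sensitivity models do not fill the gap. Most of them (rate adjustments, prokinetic or antidiarrheal use, post-pyloric feeding) can arise after randomisation and may themselves respond to the formula. Unit at randomisation cannot.

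**Working it through.** **Inputs from section 2.5.** SPF 22.4 (SD 9.825) and PBF 24.9 (SD 9.1) kcal/kg/day, so the difference is 2.5; two-sided alpha 0.05; 225 per group, 450 in total. The documents give no between-unit variance, so it is assumed below and shown as a range.

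**The plan's own figure.** Root-mean-square SD = √((9.825² + 9.1²)/2) = √89.67 = 9.47. With n per group = 2(z₁₋α/₂ + z₁₋β)² × SD²/difference²:
- 90% power: 2 × (1.960 + 1.282)² × 89.67/6.25 ≈ 302.
- 80% power: 2 × (1.960 + 0.842)² × 89.67/6.25 ≈ 226.

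The stated 225 per group therefore corresponds to about 80% power (79.96%), not the stated 90%. That is a separate and larger matter. It is noted here only because the power figures below start from 80.0%.

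**Share of variance due to unit.** Share = SD_unit²/89.67. Equivalent patients = 450 × share/(1 − share).

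| Assumed SD of unit means (kcal/kg/day) | Share of variance | Equivalent patients of 450 |
|---|---|---|
| 1 | 1/89.67 = 1.1% | 5 |
| 2 | 4/89.67 = 4.5% | 21 |
| 3 | 9/89.67 = 10.0% | 50 |

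**Power at 225 per group with unit as a fixed effect.** The residual SD becomes 9.47 × √(1 − share).

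| Share | Power | n per group for 90% power |
|---|---|---|
| 0 | 80.0% | 302 |
| 2% | 80.7% | 296 |
| 5% | 81.9% | 287 |
| 10% | 83.9% | 272 |

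**Chance imbalance.** With individual randomisation, unit imbalance adds a random error to the treatment difference with SD of about 2 × SD_unit/√450 = 0.094 × SD_unit. That is 0.09, 0.19 or 0.28 kcal/kg/day for unit SDs of 1, 2 or 3. The full standard error is 9.47 × √(2/225) = 0.89. This is the same loss seen from another side, not a further one.

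**Simulation.** N = 450, three units of equal expected size, unstratified blocks of 4 and 6, robust standard errors, no other covariates, 4,000 runs per setting.
- Type I error without the unit term was 4.9% to 5.2% for shares from 0 to 10%, and the mean estimates showed no bias.
- Power without versus with the unit term was 79.7% vs 81.8% at a 5% share and 80.7% vs 83.9% at 10%. At 2% there was no visible gain (80.0% vs 79.8%, within simulation error).
- If randomisation were in fact stratified by unit, leaving unit out would make the test conservative: type I error 3.7% at a 10% share.

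**The case against.** The strongest reply is that the modelling decision itself is sound. The sentence explains why there is no random effect, and with three units a random effect would be poorly estimated anyway. Patients, not units, are randomised. This stands.

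Nor does the article show that unit predicts intake. The limitation says that team practice *could* matter and never equates teams with units. The nutrition protocol in section 2.6.3 sets the same targets and guideline for everyone, and the Discussion expects a single centre to make feeding more consistent. This also stands, so unit can be called plausibly prognostic and no more.

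The assumed unit SDs may be generous. For three evenly spaced unit means, the gap from highest to lowest is 2 × √1.5 × SD_unit = 2.45 × SD_unit. An SD of 3 then means a gap of 7.3 kcal/kg/day, nearly three times the 2.5 that the trial is designed to detect. The existing covariates would also already absorb any part of a unit difference that is due to case mix. The gains above are therefore upper limits for each assumed SD.

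Finally, the precision argument does not carry over to feeding intolerance and the other binary outcomes. In a logit model, adding a prognostic covariate does not narrow the standard error of the log odds ratio and typically widens it, while the conditional estimate moves away from the null.

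What the reply leaves untouched is the stated reason. The claim of no clustering structure conflicts with the three units and with the plan's own limitation, and the covariate list follows from a choice the article makes openly, not from a detail left to another document.

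**Conclusion.** A minor point: an unsupported justification, and a cheap covariate left out.

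A reader might infer that ignoring clustering makes the p value invalid, biases the estimate or calls for a design effect. The documents do not support this. Randomisation is by individual, and the simulated type I error without unit stays near 5%. A reader might also infer that unit is an established prognostic factor or is already in the data set. The article states neither.

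The possible cost is confined to precision on the primary outcome and on other continuous outcomes that vary by unit. For the primary outcome it is at most about 1% to 10% of variance for assumed unit SDs of 1 to 3 kcal/kg/day, and about 2 points of power at a 5% share, less once the existing covariates are in the model. If the units feed alike, the cost is nil. These figures rest on an assumed between-unit variance and on units of roughly equal size. A unit term would not close the gap between the stated and the actual power: even at a 10% share, 272 per group would be needed for 90%.

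**What to change.** Add unit at randomisation (three levels) as a fixed effect in the primary linear model, the continuous secondary models and the imputation model, and fix this before any comparison by arm. In the binary models, including the separately analysed components of feeding intolerance, add unit only where events are not sparse, and do not claim a narrower standard error for the log odds ratio.

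Replace the no-clustering sentence with the reason that holds: the trial runs in three units, which are too few to estimate a random effect, so unit enters as a fixed effect. The randomisation scheme and the sample size need no change for this point.

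The cost is two degrees of freedom per model, with little or no gain if the units feed alike. Unit must be captured at randomisation if it is not already recorded.

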Continuous variables will be summarized as mean ± SD if normally distributed, or as median and interquartile range (IQR, P25–P75) if not normally distributed. Between-group differences in continuous variables will be tested using the independent samples t-test for normally distributed data or the Mann–Whitney U test for non-normally distributed data. Categorical variables will be compared using the Chi-square test.

To assess whether between-group differences in caloric adequacy and tolerance reflect intrinsic physiological effects of the enteral formulas or are confounded by differences in feeding tolerance management, we will compare key nutrition-support process indicators (time to EN initiation; FIS-guided feeding-rate adjustments every 4–6 h; use of prokinetic and/or anti-diarrheal agents; post-pyloric feeding) between groups during the intervention period and will add these as covariates for adjusting confounding factors. At the same time, we will conduct sensitivity analyses to test the robustness of the results.

Sensitivity analyses will include: (I) an unadjusted GLM including only the treatment factor; (II) a covariate-augmented GLM including the prespecified covariates APACHE II score, AGI grade, BMI, primary diagnosis as well as baseline mechanical ventilation. (III) Key treatment indicators include time to initiation of enteral nutrition, feeding-rate adjustments at 4–6-h intervals based on the FIS score, use of prokinetics or antidiarrheals, and use of post-pyloric feeding. All covariates are prespecified and will be retained in the models regardless of statistical significance.

Adjusted odds ratios (ORs) with 95% confidence intervals (CIs) will be reported for binary outcomes, with standardized marginal risk differences provided as supplementary estimates. The primary endpoint will be tested at a two-sided *α* = 0.05 level without multiplicity adjustment. For prespecified secondary clinical endpoints, the false discovery rate (FDR) will be controlled at q = 0.05 using the Benjamini–Hochberg procedure based on two-sided *p* values from the specified models.

Process outcomes (such as fidelity, exposure, and contamination) will be treated as exploratory outcomes and summarized descriptively with 95% CIs; no hypothesis testing or multiplicity correction will be applied to these exploratory analyses.

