All analyses were performed using R software (version 4.4.2; R Foundation for Statistical Computing, Vienna, Austria) within RStudio (version 2024.12.1+563; Posit Software, Boston, MA, USA). Two-sided *p* values <0.05 were considered statistically significant.

Given the potential for confounding and co-interventions inherent in nutritional interventions, strong causal inferences will not be made. Primary and secondary analyses are prespecified to be interpreted as estimates of association following adjustment for predefined covariates and sensitivity analyses. Any residual between-group differences will be reported cautiously.

The robustness of between-group differences will be evaluated after adjustment for prespecified clinical covariates and key management-related variables (e.g., tolerance management and feeding strategies). Attenuation of associations after adjustment may suggest partial explanation by management factors, whereas consistency of findings across sensitivity analyses may be considered compatible with potential formula-related differences; however, all conclusions will remain cautious.

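### Feeding management recorded after randomisation is adjusted for as if it were confounding, and any attenuation is then read as explanation by management; the primary model in section 2.8.2 is not affected as written

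*Protocol article*

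**What the plan says.** Patients are randomised on study day 4, and the exposure window runs from day 4 to day 7 (Protocol article, sections 2.4 and 2.7.5.1). Section 2.8.2 sets the primary model for day-7 energy intake as treatment group plus APACHE II score, BMI, AGI grade and primary diagnosis. Secondary outcomes use the same pattern.

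The same section then asks whether differences in caloric adequacy and tolerance come from the formula or from tolerance management. It names four process indicators: time to EN initiation, FIS-guided rate adjustments, prokinetic or antidiarrhoeal use, and post-pyloric feeding. These are compared "between groups during the intervention period and will add these as covariates for adjusting confounding factors". The same four appear as item III of the sensitivity analyses, with all covariates kept whatever their significance.

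On interpretation it says: "Attenuation of associations after adjustment may suggest partial explanation by management factors". Consistent findings are taken as compatible with a formula-related difference. It also says: "Given the potential for confounding and co-interventions inherent in nutritional interventions, strong causal inferences will not be made".

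**The concern.** A variable that arises after randomisation cannot confound the comparison of randomised arms. It can be a consequence of the arm. By the protocol's own account, three of the four indicators plausibly are: intolerance prompts management in both groups (section 2.6.3), and the Discussion cites the team's earlier work in which peptide formula went with less feeding intolerance and faster achievement of targets. The expected route is formula, then tolerance, then fewer rate cuts or drugs, then more energy delivered. Feeding rate is nearly a component of the outcome.

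Conditioning on these variables answers a different question from the one randomised. The stated reading then treats a benefit acting through better tolerance, which is part of what the trial is meant to detect, as a management effect. For feeding intolerance as an outcome, rate changes guided by an FIS score come close to adjusting for the outcome itself.

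**Working it through.** **Timing.** Rate adjustments, drug use and post-pyloric feeding are taken over the intervention period, so they follow day-4 randomisation. Time to EN initiation precedes it: EN must be startable within 24–48 h of ICU admission (section 2.3.1), and everyone receives peptide formula on study days 1–3 (section 2.6). Only this one of the four is a legitimate baseline covariate.

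**Scale, from section 2.5.** The SPF group has an "intake of 22.4 ± 9.825 kcal/kg/day"; "the PBF group had 24.9 ± 9.1 kcal/kg/day". Difference = 24.9 − 22.4 = 2.5. SD = √[(9.825² + 9.1²)/2] = √89.67 = 9.47.

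The plan gives no figure for the management adjustment. Its only related figure is the sample size. "Using a two-sided *α* = 0.05 and power (1 − *β*) = 0.90", n per group = 2 × (1.960 + 1.282)² × 89.67 / 2.5² ≈ 302, against the stated 225. With 225 per group the standard error is 9.47 × √(2/225) = 0.893, and power is Φ(2.5/0.893 − 1.96) = Φ(0.84) ≈ 80%. The stated 225 is therefore not reproduced. That is a separate matter; only the 2.5 and the SD are used below.

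**Model (assumed; the documents give no path strengths).** Let T = 1 for PBF, U = unmeasured gut function (SD 1), M = management intensity (SD 1 within arm) and Y = intake:

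- M = −aT − gU + error
- Y = dT + bM + hU + error

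The total effect is d − ab, fixed at 2.5. If a share s acts through M, the direct part is d = 2.5(1 − s).

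- Regressing Y on T alone recovers the total, 2.5.
- Regressing Y on T and M: within this model the mean of U given T and M is −g(M + aT). The coefficient of T is therefore d − a·g·h = **2.5(1 − s) − a·g·h**.

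The first term loses the mediated part. The second is the bias from the shared cause. Taking a = 0.4:

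| Share through M | No shared cause (a·g·h = 0) | Moderate (g 0.5, h 3: 0.4×0.5×3 = 0.6) | Strong (g 0.7, h 5: 0.4×0.7×5 = 1.4) |
|---|---|---|---|
| 0% | 2.5 | 1.9 | 1.1 |
| 50% | 1.25 | 0.65 | −0.15 |
| 100% | 0 | −0.6 | −1.4 |

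A simulation of 496,000 records per scenario agrees within about 0.1: by row, 2.53, 1.88, 1.11; 1.26, 0.56, −0.17; 0.01, −0.62, −1.40. The unadjusted difference stayed at about 2.5 throughout. With a yes/no M (38% use in SPF, 24% in PBF) the rows were 2.5, 2.2, 1.7; 1.2, 0.9, 0.4; 0.0, −0.3, −0.8.

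**When the sign reverses (continuous M).** This needs 2.5(1 − s) < a·g·h. Without a shared cause it never happens. With the moderate one, s must exceed 1 − 0.6/2.5 = 76%; with the strong one, 1 − 1.4/2.5 = 44%.

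**Consequence for significance.** If adjustment halved the coefficient to 1.25 and the standard error stayed at 0.893 (an assumption), power at 225 per group would be Φ(1.40 − 1.96) ≈ 29%. A real effect would then often look explained.

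**The case against.** Three points deserve weight.

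First, the primary and secondary models are set out with baseline covariates only, and the primary test is unchanged: "The primary endpoint will be tested at a two-sided *α* = 0.05 level without multiplicity adjustment". This stands. A reader might infer that the primary intention-to-treat estimate is biased; the text does not support that. What remains is an ambiguity. The process-indicator paragraph says the variables will be added and that sensitivity analyses will run alongside, so it is unclear whether the management-adjusted model is itself only a sensitivity analysis.

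Second, the trial is open-label and the treating team knows the arm (section 2.4). Clinicians might manage the arms differently for reasons unrelated to tolerance, and randomisation does not prevent that. The question is legitimate, and not every management difference need be a response to tolerance. But plain covariate adjustment cannot separate clinician-driven management from response to the formula, and a shared cause would bias it either way.

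Third, the interpretation is hedged: attenuation only may suggest partial explanation, and conclusions are to stay cautious. So it is reading guidance and not a decision rule. Hedging does not correct the estimate being read, though, and calling the randomised contrast an association gives up what the design provides.

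**Conclusion.** The concern holds in limited form and should be fixed before analysis. Post-randomisation management is mislabelled as confounding, and the reading attached to the adjusted result can mislead. The certain part is structural: adjustment removes the effect acting through these variables, and any cause shared by management and intake can bias the rest.

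The size is not known. Under the assumed paths a true 2.5 kcal/kg/day becomes anything from 2.5 to −1.4. A reader might infer that adjustment must erase or reverse the formula effect. It need not: with a wholly direct effect and no shared cause nothing is lost, and reversal requires both substantial mediation and a shared cause, neither of which the documents quantify. The downward direction of the shared-cause bias also rests on the assumption that PBF lowers management intensity.

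The damage is confined to the management-adjusted models and what is concluded from them, unless the sponsor intends that adjustment to enter the primary model.

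**What to change.** In section 2.8.2:

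- State that all primary, secondary and robustness models adjust only for variables fixed before randomisation. Time to EN initiation may stay.
- Report rate adjustments, prokinetic or antidiarrhoeal use and post-pyloric feeding by arm as descriptive process outcomes, alongside fidelity, exposure and contamination, which the plan already treats this way.
- Drop the post-randomisation covariates from sensitivity analysis III, or relabel it as an exploratory mediation analysis with its assumptions stated, including those on shared causes of management and intake.
- Replace the attenuation sentence: a change after such adjustment does not show that a difference was due to management and does not bear on the robustness of the primary result.
- State that the baseline-adjusted intention-to-treat contrast estimates the effect of assignment to continue PBF versus switch to SPF.

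The cost is wording only, with no extra patients or data. The downside is losing a simple check on differential management in an open-label trial; the by-arm process report replaces it in part.
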